### Statistical analysis

Regarding the primary objective of the study, which focuses on evaluating the impact of the personalized screening model on the cumulative incidence of advanced breast cancer (stage II or higher), a series of analyses are planned. Person-years at risk and follow-up duration will be calculated for both cohorts, starting from the date of first screening and continuing until the date of censoring or the end of follow-up, whichever comes first. The follow-up duration will be truncated at the 75th percentile of available follow-up times, as determined by the criterion proposed by Puliti et al. [51].

Woman age will be calculated at the date of the first screening. Cumulative age-standardized advanced breast cancer incidence rates will be calculated for both cohorts and then compared using the incidence rate ratio (IRR) along with 95% confidence interval (95% CI). Estimation of IRRs will be obtained by multivariable Poisson regression analysis.

To address potential dissimilarities (if any) in the risk of breast cancer between the two cohorts, incidence rates from the pre-intervention period will be used. Adjusting the IRR of advanced breast cancer will involve multiplying the unadjusted IRRs by the observed/expected ratio within the observational control cohort. Calculation of 95% CIs will be performed by a bootstrap procedure.

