Both the interventional and control cohorts are studied using a two-phase design involving a pre-screening period followed by a screening period. The pre-screening phase measures the baseline incidence rate of breast cancer in women aged 45–49 years in both populations. This baseline assessment helps calculate the ratio of the incidence rate at baseline between the Veneto Region and the Emilia-Romagna Region for subsequent statistical adjustment. During the screening period, the two screening models are implemented, and cumulative incidence rates of advanced breast cancer are assessed over 3 years, 5 years and 10 years (at least). The ratio of the cumulative incidence rate in the interventional cohort to that found in the observational control cohort, adjusted for differences in incidence at baseline, is calculated. The decision to evaluate the results at three-year intervals stems from previous research that demonstrated a significant decline in the incidence of pT2-4 stage breast cancer from the third year of screening [44]. The extended follow-up duration takes into account the potential lasting preventive impact of screening beyond age 50 and incorporates the common biennial digital mammography screening procedure for women over age 50.

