### Interventional cohort

The prospective interventional cohort consists of women aged 45 years from two provinces in the Veneto Region. The enrollment phase for this cohort has been completed, with a final number of participants of 10,269 women. Participants initially met specific criteria and are now undergoing successive screening rounds with different intervals and imaging protocols until the age of 50.

During the initial screening round, participants underwent two-view digital breast tomosynthesis (DBT) of both breasts. They also completed a questionnaire on risk factors such as personal characteristics, hormonal factors, family history of breast cancer, lifestyle, and health status. Volumetric breast density (VBD) values were calculated with Volpara software from DBT images [45]. Subsequently, women with an average VBD greater than 25% were invited for supplemental ultrasound (US). Based on individual risk factors and mean VBD, we used the Tyrer-Cuzick risk model to estimate lifetime risk (LTR) for each woman [17, 22]. This risk assessment categorized women into five subgroups each recommended for a personalized screening protocol:*Low-Risk, Nondense Breasts*: Women with LTR ≤ 17% and VBD < 25% are recommended for biennial DBT screening;*Low-Risk, Dense Breasts*: Women with LTR ≤ 17% and VBD ≥ 25% are recommended for biennial DBT screening with supplemental US (DBT + US protocol);*Intermediate-Risk, Nondense Breasts*: Women with LTR between 17 and 30%, or LTR > 30% without family history, and VBD < 25% are recommended for annual DBT screening;*Intermediate-Risk, Dense Breasts*: Women with LTR between 17 and 30%, or LTR > 30% without family history, and VBD ≥ 25% are recommended for annual DBT + US screening;*High-Risk, Any Breast Density*: Women with LTR > 30% and a family history of breast cancer, are recommended for annual DBT and magnetic resonance imaging (MRI) surveillance, regardless of breast density.

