### Observational control cohort

Between 1995 and 1997, the Emilia-Romagna Region started a double-reading mammography screening programme for women aged 50–69 years, which switched from analog to digital mammography (DM) in 2010–2011. The programme was extended to women aged 45–49 years and 70–74 years in 2010, with an annual screening interval for the younger age group [46]. In the context of the RIBBS study, the observational control cohort includes women 45 years of age residing in three provinces of the Emilia-Romagna Region. These individuals participated in the annual screening programme from 2012 to 2020.

The five subgroups of the interventional cohort and the observational control cohort are depicted in Fig. 1.

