### Study limitations

Due to practical and ethical concerns, a quasi-experimental design was adopted for this study. The nonrandomized nature of our design introduces potential challenges to internal validity because of discrepancies between the nonequivalent control group and the interventional group. In addition, contextual factors may affect the expected outcome [42]. However, to address potential bias from the nonrandomized design, a comparison between the two cohorts will involve adjustment for the incidence of breast cancer observed during the pre-intervention period [42, 51, 52].

Another limitation of the study is the absence of clinical and epidemiologic data on women in the reference population. This lack of data precludes a formal adjustment for potential confounding factors.

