### Study status

In the Veneto Region, enrollment in the interventional cohort began in January 2020 and ended in December 2021, successfully enrolling a total of 10,269 women aged 45 years. Currently, these participants are regularly invited to participate in subsequent screening rounds according to the established schedule. The screening phase for this cohort will extend until December 2026, providing full coverage until women reach age 50. Thereafter, they will enter the target population of the standard two-year mammography screening programme, with routine invitations until age 69.

The observational control cohort comprises women aged 45 years who were enrolled in the annual mammography screening programme between 2012 and 2020 in three provinces of the Emilia-Romagna Region, for a total number of 43,840 women. As in the Veneto Region, when these women cross the 50-year threshold, they will become part of the population eligible for biennial mammography screening.

Follow-up evaluations will continue for at least 10 years after the enrolment in the study.

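### Age at first screening is 45 for every woman, so the age standardisation is empty, and the 75th-percentile truncation can leave the two cohorts with different follow-up spans

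*Protocol article*

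**What the plan says.** The Statistical analysis section plans that "Cumulative age-standardized advanced breast cancer incidence rates will be calculated for both cohorts", to be compared by an IRR from multivariable Poisson regression. The age variable is set in one sentence: "Woman age will be calculated at the date of the first screening". Person-years start at first screening, and "The follow-up duration will be truncated at the 75th percentile of available follow-up times", following a criterion cited from an earlier publication.

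Entry age is the same in both cohorts: "The prospective interventional cohort consists of women aged 45 years from two provinces in the Veneto Region", and "the observational control cohort includes women 45 years of age residing in three provinces of the Emilia-Romagna Region". Table 3 lists age 45 as an inclusion criterion for both.

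Entry dates differ. Study status reports that "enrollment in the interventional cohort began in January 2020 and ended in December 2021, successfully enrolling a total of 10,269 women aged 45 years". The 43,840 control women entered between 2012 and 2020.

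The Abstract and Study design set fixed horizons: "cumulative incidence rates of advanced breast cancer are assessed over 3 years, 5 years and 10 years (at least"). Table 1 instead describes the primary outcome over the whole follow-up period. The Sample size section assumes five years of exposure in each cohort. The baseline incidence used for adjustment is measured in women aged 45-49 (Study design).

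**The concern.** Age standardisation is meant to stop differences in age structure from passing as a screening effect. Here entry age does not vary, so the variable chosen has nothing to adjust. What can differ between the cohorts is attained age, which is the same as time since first screening when everyone starts at 45. Three things move along that axis: underlying incidence, the excess of cancers found at the first round, and the change to biennial screening at 50.

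This matters only if the cohorts contribute person-time over different spans. With nine years of entry on one side and two on the other, they will do so unless the truncation rule prevents it. If it does not, two equally effective programmes could give an IRR away from 1. A larger sample would not help. The study is powered for a rate ratio of 0.810, so a few per cent in either direction is not negligible.

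**Working it through.** **The plan's own figure.** Inputs from Sample size: 43,000 and 10,269 women, 5 years each, control rate 0.004017, rate ratio 0.810, one-sided alpha 0.05. Expected events are m1 = 43,000 × 5 × 0.004017 = 863.7 and m2 = 10,269 × 5 × 0.004017 × 0.81 = 167.1. With ρ = 10,269/43,000, power = Φ(2[√(ρ(m1+3/8)) − √(m2+3/8)]/√(1+ρ) − 1.645) = 82.0%, close to the stated 80.5%. The power statement therefore rests on equal five-year exposure. The point below does not otherwise affect it.

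**Age.** With a single stratum of weight 1, the standardised rate is 1 × the crude rate, whatever the standard population.

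**Follow-up spans.** Assumptions: uniform entry, no attrition, and first cut-offs at the ends of the screening phases given under Pre-screening and screening periods (2024 control, 2026 interventional). Follow-up is then 4-13 years in control and 5-7 in the interventional cohort.
- Per-cohort 75th percentiles: 4 + 0.75 × 9 = 10.75 and 5 + 0.75 × 2 = 6.5 years.
- Pooled 75th percentile c: a quarter of 54,109 women (13,527) lie above it, all in control. So c = 13 − 9 × 13,527/43,840 = 10.2 years, and no interventional woman is truncated.
- Mean follow-up, pooled cut: control 10.22 − (10.22 − 4)²/18 = 8.07; interventional 6.0.
- Mean follow-up, one cut at 6.5: control 6.5 − (6.5 − 4)²/18 = 6.15; interventional 6.5 − (6.5 − 5)²/4 = 5.94.
- Under the pooled cut, about 19.5% of control person-years lie beyond 7 years, where the interventional cohort has none. About 39% of control and 17% of interventional person-years lie beyond 5 years, that is, above age 50.

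**IRR when the programmes are equivalent.** The documents give neither an age trend nor a first-round excess, so both are assumed: incidence rising 3-5% per year, or a first-round peak worth k = 1-2 years of incidence. For the peak alone, IRR = (1 + k/mean_I)/(1 + k/mean_C), with mean_I and mean_C the mean follow-up in the interventional and control cohorts. Pooled: k = 1 gives 1.1667/1.1239 = 1.038, and k = 2 gives 1.3333/1.2478 = 1.069. For the slope s, each woman followed for t years contributes ((1+s)^t − 1)/ln(1+s) expected events (baseline rate 1); each cohort's events are summed and divided by its person-years.

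| Cut-off (interventional / control) | Percentile read as | Maximum years, I / C | Slope 3% to 5% | Peak 1 to 2 years | Both together |
|---|---|---|---|---|---|
| end 2026 / end 2024 | pooled | 7.0 / 10.2 | 0.961 to 0.935 | 1.038 to 1.069 | 0.972-1.030 |
| | per cohort | 6.5 / 10.75 | 0.957 to 0.927 | 1.042 to 1.075 | 0.968-1.032 |
| | one shorter cut | 6.5 / 6.5 | 0.996 to 0.994 | 1.005 to 1.009 | 0.999-1.005 |
| both end 2026 | pooled | 7.0 / 12.2 | 0.933 to 0.889 | 1.061 to 1.112 | 0.945-1.041 |
| | one shorter cut | 6.5 / 6.5 | 0.992 to 0.987 | 1.012 to 1.022 | 0.999-1.014 |
| both end 2031 | pooled | 12.0 / 17.2 | 0.934 to 0.888 | 1.023 to 1.043 | 0.909-0.975 |

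**Fixed horizons.** At 3 years all these cut-offs give 1.00. At 5 years the ratio is 1.00 with both cohorts closed at end 2026, and within 0.003 of 1 with control closed at end 2024. At 10 years it is 1.00 once both are followed to end 2031; at end 2026 the interventional cohort has at most 7 years.

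**The case against.** A reader might infer that the truncation rule necessarily leaves the cohorts on different spans. The text does not support that. It does not say whether the percentile is pooled, per cohort or a single common value, and the cited criterion is not reproduced. Under one cut at the shorter cohort's value the null IRR stays within about 0.99-1.02. The fixed horizons in the Abstract and Study design also already equalise the spans once every woman has reached them, and at equal spans an empty age standardisation does no harm.

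A reader might also infer a bias of known direction. A rising incidence pulls the IRR down and a first-round peak pushes it up. With the 2024 and 2026 cut-offs the combined range is only about 0.97-1.03. Those dates moreover end the screening phase, not follow-up, which Study status extends to at least ten years. This objection stands as far as it goes, but the cancellation is not general: with both cohorts followed to end 2031, a pooled cut gives 0.91-0.98 for the combined scenarios.

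Finally, it is tempting to call the planned IRR a crude person-year ratio. Study limitations does say "This lack of data precludes a formal adjustment for potential confounding factors", but that concerns missing clinical and epidemiologic data. Entry dates are held, so time since entry could be modelled, and an article may leave the covariate list to the analysis plan. What the article does specify is the age variable, and that one cannot adjust for anything.

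**Conclusion.** The age standardisation as specified is empty. This follows from the eligibility criteria and needs no assumption. The truncation rule is ambiguous and is not reconciled with the 3-, 5- and 10-year horizons or with Table 1. Two of its three readings leave unequal spans: about 10.2 v 7 years (pooled) or 10.75 v 6.5 years (per cohort), given uniform entry, no attrition and cut-offs at end 2024 and end 2026.

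The possible distortion of the primary IRR is moderate and uncertain in direction: about 0.93-1.07 with one assumed mechanism at a time, 0.89-1.11 with a common end-2026 cut-off, and smaller where the two mechanisms offset each other. The age slopes and first-round peaks are assumptions, not figures from the article. This should be corrected before the analysis. It does not show that the planned result will be biased.

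**What to change.** In the Statistical analysis section:

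1. For the primary comparison, replace the percentile truncation with the same fixed horizon in both cohorts, using the 3, 5 and 10 years already set in Study design. Analyse each horizon once all women can reach it. With the last interventional entry in December 2021, that means end 2024, end 2026 and end 2031. Control follow-up for the 5-year horizon must then run to end 2025, one year past the end of its screening phase. Align the wording of Table 1.
2. Replace age at first screening with attained age (here, time since first screening) as a time-varying stratum in the Poisson model, with person-time split accordingly.
3. For person-time above age 50, do not rely on the 45-49 baseline ratio alone. Use a ratio specific to the age band where registry data allow.

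The cost is a change of wording and routine person-time splitting, using the entry dates and registry linkage already planned. The downside is that some late control person-time goes unused at each horizon.

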### Dissemination plan

The results of the study will be widely disseminated through rigorous publications in reputable peer-reviewed journals. In addition, results will be communicated through presentations at regional, national, and international workshops and conferences. The dissemination strategy will primarily target clinicians, researchers and crucial stakeholders, including scientific societies and the Italian regional healthcare authorities. To ensure transparency and adherence to reporting standards, the study will adhere to the 'REporting of studies Conducted using Observational Routinely collected health Data' (RECORD) guidelines.

## Discussion

This study represents a novel exploration into the impact of a personalized screening strategy, tailored according to breast density and risk, on the cumulative incidence of advanced breast cancer and other standard screening performance metrics among young women.

The study is particularly relevant because of the growing consensus on lowering the age of entry in breast cancer screening to 45 years and the ongoing worldwide debate about moving from a uniform age-based model to personalized, woman-centered approaches.

A key strength of this project is the innovative approach to personalizing breast cancer screening. A screening programme was developed for the interventional cohort, taking into account both breast density and cancer risk, two critical factors in personalizing screening. For women with dense breast, the inclusion of ultrasound complements annual or biennial DBT to mitigate the limitations of X-ray imaging. In addition, the screening interval for low-risk women has been increased. Stratification of density and risk is based on objective data, including volumetric breast density and lifetime risk derived from relevant risk factors.

In summary, we believe that the methods employed provide a valid and pragmatic means of evaluating the effectiveness and feasibility of a screening procedure stratified by breast density and risk in real-world settings.

### Study limitations

Due to practical and ethical concerns, a quasi-experimental design was adopted for this study. The nonrandomized nature of our design introduces potential challenges to internal validity because of discrepancies between the nonequivalent control group and the interventional group. In addition, contextual factors may affect the expected outcome [42]. However, to address potential bias from the nonrandomized design, a comparison between the two cohorts will involve adjustment for the incidence of breast cancer observed during the pre-intervention period [42, 51, 52].

Another limitation of the study is the absence of clinical and epidemiologic data on women in the reference population. This lack of data precludes a formal adjustment for potential confounding factors.

### Study status

In the Veneto Region, enrollment in the interventional cohort began in January 2020 and ended in December 2021, successfully enrolling a total of 10,269 women aged 45 years. Currently, these participants are regularly invited to participate in subsequent screening rounds according to the established schedule. The screening phase for this cohort will extend until December 2026, providing full coverage until women reach age 50. Thereafter, they will enter the target population of the standard two-year mammography screening programme, with routine invitations until age 69.

The observational control cohort comprises women aged 45 years who were enrolled in the annual mammography screening programme between 2012 and 2020 in three provinces of the Emilia-Romagna Region, for a total number of 43,840 women. As in the Veneto Region, when these women cross the 50-year threshold, they will become part of the population eligible for biennial mammography screening.

Follow-up evaluations will continue for at least 10 years after the enrolment in the study.

## Data Availability

Not applicable.

## Abbreviations

BC: Breast cancer
BI-RADS: Breast imaging reporting and data system (American College of Radiology)
BMI: Body mass index
CI: Confidence interval
DBT: Digital breast tomosynthesis
DM: Digital mammography
H0: Null hypothesis
Ha: Alternative hypothesis
IOV: Veneto Institute of Oncology
IRR: Incidence rate ratio
LTR: Lifetime risk
MRI: Magnetic resonance imaging
RIBBS: Risk-based breast screening
RRa: Event rate ratio under the alternative hypothesis
US: Ultrasound
VBD: Volumetric breast density
